### Patient assessments

Heart rate, blood pressure, and body temperature will be documented hourly for the first 24 h after treatment start and every 12 h thereafter in both treatment groups, and additionally at every dose change of landiolol in the landiolol group. Clinical laboratory analysis including blood gas analysis will be performed daily for the first four days of the study. Sequential Organ Failure Assessment (SOFA) score will be assessed daily for the first four days and every third day thereafter. If performed, hemodynamic parameters (CO, CI, GEDI, ELWI, PAOP, MPAP, LVEF, TAPSE, VTI) obtained by PICCO/FloTrac, Swan-Ganz catheter or Cardiac Echo will be documented. Concomitant medication and AE will be documented over the entire study period. Measurements and assessments performed in both groups are listed in Fig. 1 in the completed SPIRIT figure.

**Fig. 1 Fig1:**
[figure not shown]
Schedule of enrolment and assessments (SPIRIT 2013 Figure)

### Endpoints

The primary efficacy endpoint is HR response (HR = 80–94 bpm) and maintenance thereof without increase in vasopressor requirements during the first 24 h after treatment start.

Secondary efficacy endpoints will consist of ICU and 28-day mortality, ICU and hospital stay duration, SOFA score, and inotrope and vasopressor support requirements. Efficacy and safety endpoints are listed in Table 3.

**Table 3 Tab3:** Efficacy and safety endpoints

Primary endpoint: • HR response (i.e. HR = 80–94 bpm) and maintenance thereof and no increase in vasopressor requirements during the first 24 h after treatment start Secondary endpoints: • Change in vasopressor requirements over the study period (dose and duration) • HR response (i.e. HR = 80–94 bpm) during the first 24 h after treatment start • 28-day mortality (all cause) • ICU mortality (all cause) • Duration of ICU stay (survivors/non-survivors) • Duration of hospital stay (survivors/non-survivors) • SOFA score (as long as the patient is treated with vasopressors) on days 1, 2, 3, 4, 7, 10, 13, 16, 19, 22, 25, and 28 • Daily inotropic requirements (as long as the patient is treated with vasopressors) Safety endpoints: • Incidence rate of bradycardic episodes requiring intervention • Incidence of adverse events (AE) • Incidence of serious adverse events (SAE)	

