### Randomization, blinding, and treatment allocation

Patients fulfilling the selection criteria are randomized in a 1:1 ratio to one of the two groups (landiolol or control) after informed consent, as required by local law, has been obtained. The presence of atrial fibrillation in the hemodynamic optimization period is used as a stratification factor for randomization. As this is an open label study, investigators and other study personnel will not be blinded to the treatment.

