### Treatments

#### Landiolol group

Patients in the landiolol group begin continuous infusion with landiolol within 2 h after randomization at a starting dose of 1 mcg/kg/min. The dose is to be progressively increased at increments of 1 mcg/kg/min to a maximum of 40 mcg/kg/min at intervals of at least 20 min to obtain and maintain a HR of 80–94 bpm. Landiolol must be infused continuously to maintain the target HR until one the following events occurs: discontinuation of vasopressor infusion; death; a serious adverse event (AE) attributable to the study drug that necessitates study drug discontinuation as determined by the investigator; patient discharge from the ICU; or day 28 of study participation.

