#### Control group

Patients in the control group receive standard of care treatment according to the Surviving Sepsis Campaign Guidelines 2016 [40], which does not specify a target for HR control. Patients in the control group are to be withdrawn from the study if they receive beta-blocker treatment.

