Esmolol is the beta-blocker that has been most frequently evaluated in patients with sepsis, as its pharmacokinetic profile allows for rapid titration when used intravenously [10, 27–29, 31]. However, landiolol has demonstrated a more favorable pharmacokinetic and pharmacodynamic profile than esmolol [52–55]. Landiolol has a faster onset (1 min vs 2 min) and shorter half-life (4 min vs 9 min) than esmolol, which should allow for more rapid titration and enhanced safety [35]. Furthermore, the beta1 selectivity of landiolol is eight times higher than that of esmolol, resulting in a beta1/beta2 ratio of 255 [35]. This provides landiolol with more profound negative chronotropic effects and a lesser degree of negative inotropic and hypotensive action [36–38, 56].

This study will investigate whether HR control using the short-acting beta-blocker landiolol is feasible, safe, and effective in patients with septic shock and persistent tachycardia, and provide a better understanding of the potential role of beta-blockers in this patient population.

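### The bradycardia safety endpoint counts only episodes that require intervention, in an open-label trial where one arm alone has an infusion to turn down, so it is open to differential ascertainment and needs an arm-neutral companion

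*Protocol article*

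**What the plan says.** The Endpoints section of the protocol article (Table 3) names three safety endpoints. One is specific to the pharmacology of the drug: "Incidence rate of bradycardic episodes requiring intervention". The other two are the overall incidences of adverse events and of serious adverse events.

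Four other statements bear on how this endpoint will be counted:

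- Randomization, blinding, and treatment allocation: "As this is an open label study, investigators and other study personnel will not be blinded to the treatment".
- Landiolol group: a continuous infusion titrated to a heart rate of 80–94 bpm. "The dose is to be progressively increased at increments of 1 mcg/kg/min to a maximum of 40 mcg/kg/min".
- Control group: guideline care "which does not specify a target for HR control", with no study infusion. A control patient given a beta-blocker is withdrawn.
- Patient assessments: heart rate is "documented hourly for the first 24 h after treatment start and every 12 h thereafter in both treatment groups". The landiolol arm has further readings whenever the dose changes.

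The Discussion presents the short action of landiolol as a safety feature: "shorter half-life (4 min vs 9 min) than esmolol, which should allow for more rapid titration and enhanced safety".

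**The concern.** An episode enters this endpoint only if it is judged to require action. Those who judge know the arm, and the actions open to them differ by arm. In the landiolol arm an infusion with a 4 min half-life can be lowered or stopped. In the control arm there is no such infusion. The same low heart rate can therefore be counted in one arm and not in the other.

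This follows from the endpoint as stated, and not merely from a definition that a condensed article may leave to the full protocol or the SAP. The counting can differ by arm whichever way intervention is defined; only the form of the problem changes.

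At stake is the reading of the one safety endpoint aimed at the expected harm of a beta-blocker, in a trial whose abstract and Discussion both ask whether heart rate control is safe. A difference in this endpoint could partly reflect how staff responded, and the absence of a difference could hide low heart rates that were corrected by titration.

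**Working it through.** **The plan's own figures.** None is given for bradycardia. The only design figure is the sample size for the primary endpoint (60% versus 40%, alpha 0.05, 80% power, 200 patients). It reproduces: the pooled two-proportion formula without continuity correction gives 97 per arm, 194 in all, and 100 per arm gives 81.2% power. It has no bearing on bradycardia except to fix about 100 patients per arm.

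**Two readings of intervention, set against the stated design.**

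1. *Dose reductions and stops count.* Only the landiolol arm can produce this kind of event, so the likely error is over-counting on landiolol.
2. *They do not count.* The landiolol arm then has an extra, uncounted remedy. Low heart rate caused by the drug and reversed by down-titration never reaches the endpoint. The Landiolol group section describes only upward steps. That the dose is also reduced is my inference from the 80 bpm floor of the target range and from the Discussion's argument on titration.

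**Illustration. All risks and shares below are assumptions; none is in the documents.** Let b be the true risk of at least one low-heart-rate episode and q the share counted as requiring intervention. The observed proportion is b × q. For simplicity I count patients, not episodes.

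*Reading 1, equal true risk in both arms, 100 per arm.* The chance of a nominally significant difference (two-sided 5%) is

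Φ{ [ |pL − pC| − 1.96 √(2p̄(1 − p̄)/n) ] / √([pL(1 − pL) + pC(1 − pC)]/n) }, with n = 100 and p̄ the mean of pL and pC.

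| True risk b | q landiolol | q control | Observed | Ratio | Chance of a spurious difference |
|---|---|---|---|---|---|
| any | 0.50 | 0.50 | equal | 1.0 | nominal level |
| 10% | 0.75 | 0.50 | 7.5% vs 5% | 1.5 | about 11% |
| 5% | 1.00 | 0.50 | 5% vs 2.5% | 2.0 | about 15% |
| 10% | 1.00 | 0.50 | 10% vs 5% | 2.0 | about 27% |
| 20% | 1.00 | 0.50 | 20% vs 10% | 2.0 | about 51% |
| 20% | 1.00 | 0.25 | 20% vs 5% | 4.0 | about 90% |

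The normal approximation is rough where only a few events are expected.

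*Reading 2, true risk 20% versus 5% (15 points, ratio 4.0), with 25% of control episodes counted.* Controls show 0.05 × 0.25 = 1.25%.

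- If 80% of landiolol episodes resolve on dose reduction and the rest are counted: 0.20 × 0.20 = 4%. The difference is 2.75 points and the ratio 4/1.25 = 3.2.
- If 50% resolve: 0.20 × 0.50 = 10%. The difference is 8.75 points and the ratio 10/1.25 = 8.0.
- With the same 25% share in both arms: 0.20 × 0.25 = 5% versus 1.25%. The difference is 3.75 points and the ratio 4.0.

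The last line separates two effects. Most of the fall from 15 to 2.75 points comes from restricting the count to treated episodes, which applies to both arms. The differential part is the step from 3.75 to 2.75 points. When half resolve, the differential part goes the other way, from 3.75 to 8.75 points. Under this reading neither the size nor the direction of the distortion in the between-arm contrast is fixed. What is certain is that the reversed episodes are absent from the count.

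**The case against.** The strongest reply has four parts.

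- *The definition is out of sight.* The article condenses protocol version 3.0. The bradycardia threshold and the meaning of intervention may well be given there or in the SAP, and their absence here is no fault. This stands. It limits what can be said about the size, but not the observation that the endpoint depends on unblinded action.
- *Counting only treatment beyond titration is legitimate.* Fast titration is part of the landiolol regimen, and comparing bradycardia that needs more than a dose change is a fair, narrower contrast between strategies. A need for intervention is also a sensible filter for clinical relevance. This stands, and is why the endpoint should be kept.
- *Other capture exists.* Adverse events and serious adverse events carry no intervention condition, and adverse events are recorded throughout the study. This stands in part: both are overall incidences, reported by staff who know the arm. Hourly heart rate is collected, but no listed safety endpoint uses it.
- *A heart rate count is not a better endpoint.* Hourly readings can miss episodes that resolve in minutes. They stop after 24 h, whereas landiolol may run to day 28. A cut-off near 80 bpm would count successful rate control as harm. This stands against replacing the endpoint, but not against a companion.

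A reader might infer that the rates in the two arms are not comparable, or that the comparison is biased under either definition. The documents do not support that: with equal counted shares there is no distortion, and the second reading yields a narrower question, not necessarily a wrong answer.

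**Conclusion.** The point holds as a risk of differential ascertainment. Table 3 makes the one drug-specific harm endpoint depend on an intervention judged by unblinded staff, and only one arm has an infusion to reduce. The likely consequence is over-counting on landiolol if dose changes count, and missed drug-induced low heart rate if they do not.

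Its size cannot be derived from the documents. In the illustration it runs from no distortion to a fourfold ratio with equal true risk, entirely according to the assumed counted shares. The consequence is limited: the endpoint is not confirmatory, and the primary analysis does not use it. It would also be too strong to say that the trial's whole answer on safety turns on this line, since adverse events, serious adverse events and vasopressor requirements are assessed too.

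The change is worth making because it is cheap and makes the bradycardia comparison less dependent on decisions taken with the arm known.

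**What to change.** Keep the endpoint and make two additions, in the SAP before it is finalized (the Statistical analysis section shows that this was still to come).

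1. Report it in two parts: interventions possible in both arms, compared between arms; and landiolol dose reductions or stops for low heart rate, described for the landiolol arm only.
2. Add as a companion the proportion of patients in each arm with at least one heart rate below a prespecified bradycardia cut-off. The sponsor sets the cut-off, clearly below the 80 bpm floor of the target range. Use only the hourly readings of the first 24 h that both arms share, and leave out the extra readings at landiolol dose changes, which would give that arm more chances to record a low value.

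Cost: endpoint wording and one table. The companion needs no new data, because hourly heart rate is already recorded in both arms. For the split, the sponsor should confirm that the reason for a dose change and any non-drug intervention are recorded; the article does not say.

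Downside: some readings without clinical consequence will be counted, and brief episodes or those after 24 h will be missed. For that reason the companion stands beside the existing endpoint and does not replace it.

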### Data collection

Data will be collected and entered into the electronic data capture system by trained study personnel (investigators and study nurses).

### Sample size

Sample size estimation is based upon the assumption that 60% of patients in the landiolol group reach the primary endpoint versus 40% of patients in the control group. The sample size of 200 patients will provide 80% power to demonstrate a statistically significant difference (upon standard level alpha = 0.05) between the treatment groups using a Chi-square test. The sample size in the study by Morelli et al. [10] was adequate considering that to detect a 20% change in HR with a power of 80% at a level of significance of alpha = 0.05, 64 patients per group would have been required. In order to detect the binary primary endpoint of our study an additional 36 patients per group are required.

### Statistical analysis

The hypothesis that Group L is superior to Group C in proportion of patients who reached the primary endpoint will be demonstrated if the lower limit of the two-sided 95% Newcombe confidence interval of difference pL-pC is above zero, where pL and pC are percentages of patients who reached the primary endpoint in Group L and Group C, respectively. *P* values based on Cochran–Mantel–Haenszel (according to SAS® terminology) will be presented together with the confidence intervals to evaluate statistical significance of association between treatment group and outcome after adjustment for the stratification group. For the purpose of exploratory analysis, the individual criteria of the primary endpoint, heart rate response (i.e. HR = 80–94 bpm) reached (also defined as secondary endpoint), heart rate response reached and maintained and no increase in vasopressor requirements during the first 24 h, will be compared separately between treatment groups. Additional subgroup and sensitivity analyses will have exploratory character and will be defined in all details in the SAP.

Secondary endpoints with continuous, ordinal, and binary variables measured at multiple time-points will be analyzed as longitudinal data by linear, ordinal logistic, logistic, or log-binomial regression models with repeated measures. Covariates used in the models will be (but not limited to) treatment, visit, stratification group, and interaction treatment/visit. For continuous variables baseline value of the outcome variable will be a covariate as well. Distribution of data and a feasibility check of planned analyses will be performed before finalization of SAP and alternative statistical methods will be defined if assumptions on the application of the planned methods are not met (e.g. ln-transformation of data, non-parametric method, or other alternative way). ICU mortality and 28-day mortality will be analyzed using the same methods as for the primary endpoint. Duration of ICU stay and duration of hospital stay (in survivors/non-survivors) will be analyzed as time-to-event data (using Kaplan–Meier curve and using log-rank test or Wilcoxon test and/or proportional hazards regression model if appropriate).

For secondary analyses, no multiplicity adjustment is planned; therefore, a higher rate of type-I error must be considered in interpretation of results of secondary analyses. The analysis of secondary endpoints/analyses can provide supportive evidence related to the primary objective, but no confirmatory conclusion based on secondary analyses can be done.

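### The deciding Newcombe interval ignores the atrial fibrillation stratum used for randomisation; if that stratum is prognostic, the rule is mildly conservative and can fail while the adjusted CMH P value is below 0.05

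*Protocol article*

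**What the plan says.** - **Randomisation** (Randomization, blinding, and treatment allocation): "Patients fulfilling the selection criteria are randomized in a 1:1 ratio to one of the two groups", and "The presence of atrial fibrillation in the hemodynamic optimization period is used as a stratification factor for randomization".
- **Decision rule** (Statistical analysis): superiority is shown if the "lower limit of the two-sided 95% Newcombe confidence interval of difference pL-pC is above zero". pL and pC are the plain percentages of responders in each group. No stratum or weight enters.
- **Companion test** (same section): CMH P values, adjusted for the stratification group, are presented with the interval. They are not part of the criterion.
- **Other endpoints** (same section): ICU and 28-day mortality are analysed by the methods of the primary endpoint. The repeated-measures models for secondary endpoints include the stratification group, and for continuous outcomes also the baseline: "For continuous variables baseline value of the outcome variable will be a covariate as well".
- **Sample size** (Sample size): the assumption is "60% of patients in the landiolol group reach the primary endpoint versus 40% of patients in the control group". On that assumption, 200 patients are said to give 80% power for a difference "between the treatment groups using a Chi-square test", which is unstratified.

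**The concern.** Stratified randomisation balances AF between the groups, which removes one source of chance variation from pL − pC. An interval built from overall percentages still counts that variation, so it is somewhat too wide if AF predicts the endpoint. AF is the only stratification factor named and the endpoint is a heart-rate response, so a prognostic effect is plausible.

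Two things are at stake on the only confirmatory comparison. Some precision that the design has already secured may be thrown away. Readers may also be shown a significant adjusted P value beside an interval that includes zero. The mortality endpoints inherit the same mismatch.

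**Working it through.** **1. The plan's own figure.** Inputs: 60% vs 40%, 100 per group (200 at 1:1), two-sided alpha 0.05.

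Power = Φ{[0.20 − 1.96·√(2·0.5·0.5/100)] / √[(0.6·0.4 + 0.4·0.6)/100]} = Φ{(0.20 − 0.1386)/0.0693} = Φ(0.886) = 81.2%.

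The formula needs 97 per group for 80%. The stated 80% with 200 patients is reproduced. By exact enumeration without strata, the crude Newcombe rule and the chi-square test both have 82.6% power and practically never disagree. The planned power therefore applies to the rule as written.

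**2. Why a prognostic stratum makes the crude rule conservative.** Let f be the AF share, p1 and p0 the response with and without AF, and p the overall response. The crude variance per patient is p(1−p). With balance on AF, the variance that applies is p(1−p) − f(1−f)(p0−p1)². With no treatment effect and p = 0.40, p(1−p) = 0.24. The effective critical value is 1.96·√[0.24/(0.24 − f(1−f)(p0−p1)²)].

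The article gives neither f nor p1 and p0. The following are assumptions, each set so that overall control response is 40%:

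| AF share | Control response, AF vs no AF | AF odds ratio | f(1−f)(p0−p1)² | Critical value | One-sided error |
|---|---|---|---|---|---|
| 30% | 20% vs 48.6% | 0.26 | 0.0172 | 2.03 | 2.1% |
| 40% | 20% vs 53.3% | 0.22 | 0.0266 | 2.08 | 1.9% |
| 30% | 10% vs 52.9% | 0.10 | 0.0386 | 2.14 | 1.6% |

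**3. Simulation of the same scenarios.** 200,000 trials each, 200 patients, balanced within stratum, 20-point difference in each stratum. CMH was run without continuity correction.

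| Scenario | Crude one-sided error | Power, crude rule | Power, CMH | CMH significant, crude interval includes zero |
|---|---|---|---|---|
| 1 | 2.1% | 83.5% | 83.8% | 0.35% |
| 2 | 1.95% | 83.9% | 85.3% | 1.4% |
| 3 | 1.65% | 84.7% | 87.6% | 2.9% |

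**4. Weaker AF effects.** Power for crude rule vs CMH, overall rates held at 60% vs 40%:
- Odds ratio 1: about 82.6% for both (AF share 20–50%), with crude one-sided error about 2.6%.
- Odds ratio 0.6: the same for both, 82.8–82.9% (AF share 30–40%).
- Odds ratio 0.5: difference of 0.03 points or less (AF share 20–50%).
- Odds ratio 0.4: 83.1% vs 83.1–83.2% (AF share 30–40%).
- Odds ratio 0.33: CMH gains 0.1–0.4 points (AF share 20–50%).

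**5. One data set, two answers.** Landiolol vs control: AF 8/30 vs 3/30, no AF 45/70 vs 37/70, so 53/100 vs 40/100 overall.
- *Crude Newcombe.* The Wilson lower limit for 53/100 is 0.4329 and the upper limit for 40/100 is 0.4980. Lower limit = 0.13 − √[(0.53 − 0.4329)² + (0.4980 − 0.40)²] = −0.008. Superiority is not shown.
- *CMH.* Observed minus expected is 2.5 + 4.0 = 6.5. The variance is 2.284 + 8.554 = 10.838. z = 6.5/√10.838 = 1.974, P = 0.048.
- *Square-and-add stratified Newcombe, Mantel–Haenszel weights 0.3 and 0.7.* The squared distances sum to (0.2667 − 0.1418)² + (0.2562 − 0.1000)² = 0.0400 with AF and (0.6429 − 0.5259)² + (0.6410 − 0.5286)² = 0.0263 without. Lower limit = 0.13 − √(0.09·0.0400 + 0.49·0.0263) = 0.13 − 0.1284 = +0.002. This agrees with CMH.

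**6. The form of the stratified interval matters.** In the three scenarios, a form that takes the variance as L(1−L) at stratified Wilson limits (the Yan–Su type) had the same power as the crude rule: 83.5, 83.9 and 84.7%. CMH was still significant with that interval including zero in 0.35, 1.4 and 2.9% of trials. The square-and-add form recovered most or all of the gain and disagreed with CMH in 0.2–0.5% of trials.

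**The case against.** The strongest reply is that the plan is coherent as it stands. It has one criterion, the interval. The CMH P value only accompanies it, so a split result is already resolved. A reader might infer that the plan contradicts itself; the text does not support that. The sample size rests on an unstratified test that the crude rule matches almost exactly, so a reader who infers an underpowered trial would also be wrong. This part of the reply stands.

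A reader might also infer that the rule is conservative and loses power whatever the data. That does not follow. The loss depends on AF being strongly prognostic, and the article says nothing on this. With odds ratios of 0.33 or weaker, the loss is under half a point.

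A third tempting reading is that leaving baseline heart rate and norepinephrine dose out of the primary analysis is an error. It is not. Any gain rests on assumed effects, and the article defers sensitivity analyses to the SAP, which is not shown.

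The reply does not remove the basic point. The article states its decision rule explicitly, and that rule leaves out the factor the trial randomises by. The SAP may already specify a stratified interval. If so, only the article's wording needs aligning.

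**Conclusion.** The point holds as a small, conditional improvement and does not threaten validity. As written, the deciding interval is crude while randomisation and the accompanying test use AF.

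With an assumed AF odds ratio of about 0.26 to 0.10 and an AF share of 30–40%, the costs are those in the simulation table: a one-sided error of about 1.6–2.1% instead of 2.5%, about 0.3–3 points of power, and a split result in about 0.3–3% of trials. With a weak or absent AF effect the cost is nil. Type I error is not materially inflated and power stays above the stated 80% throughout. The direction is certain if AF is prognostic. The size is not known from the document.

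**What to change.** Before any outcome data are seen, specify one AF-stratified result as the primary decision:

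- either the CMH test itself (two-sided P below 0.05 in favour of landiolol),
- or the lower limit of an interval for the Mantel–Haenszel common risk difference, with variance built within strata. An example is the square-and-add stratified Newcombe form.

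Name the form in full. A version that applies L(1−L) to the pooled limits brings no gain, so a general reference to a stratified Newcombe interval is not enough. State that this one result decides and that any other is supportive. Use the same interval for ICU and 28-day mortality.

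The cost is a sentence or two in the analysis plan and a check that the software computes the named form. No patients or data items are added. If AF proves not to be prognostic, practically nothing is lost. At an AF share of only 10%, CMH power was at most about 0.2 points below the crude rule.

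A covariate-standardised risk difference using baseline heart rate and norepinephrine dose may be added as an optional supplementary analysis.

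### Mortality is analysed with an interval that names no covariates and a P value adjusted only for atrial fibrillation, so prognostic data known at entry go unused: valid, but modestly less precise than it need be

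*Protocol article*

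**What the plan says.** Under Statistical analysis, the article states that "ICU mortality and 28-day mortality will be analyzed using the same methods as for the primary endpoint". For the primary endpoint, superiority is shown if "the lower limit of the two-sided 95% Newcombe confidence interval of difference pL-pC is above zero", and CMH P values accompany the interval to assess "association between treatment group and outcome after adjustment for the stratification group". No covariate is named for the interval. Under Randomization, blinding, and treatment allocation there is a single stratification factor: "The presence of atrial fibrillation in the hemodynamic optimization period is used as a stratification factor for randomization".

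Other secondary endpoints are treated differently in the same section. The repeated-measures models have an open covariate list, and continuous outcomes carry their baseline value. Length of stay may use a proportional hazards model.

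On entry data, Table 2 requires age of at least 18 years and a norepinephrine rate of at least 0.2 μg/kg/min at inclusion, with no upper limit stated. Under Patient assessments, "Sequential Organ Failure Assessment (SOFA) score will be assessed daily for the first four days and every third day thereafter". The section closes by making all secondary analyses supportive, without multiplicity adjustment and without confirmatory conclusions.

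**The concern.** The mortality method is positively specified, so it is not a gap left to the SAP. It carries over to death a method set up for a 24-hour heart-rate endpoint. Death in septic shock can be expected to depend on how ill the patient is at entry, and nothing in the design balances that. The only stratum is a rhythm factor.

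Entry severity can also vary widely. Norepinephrine has a floor but no ceiling. The footnote to Table 2 allows the lactate and SOFA criteria to have been met before inclusion and no longer be present, so patients in full shock and patients partly recovered can both enter.

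Two things are at stake. The mortality interval is wider than the available data require. And if the arms differ in severity by chance, the plan holds no pre-specified adjusted estimate to set beside the crude one. Covariates chosen after an imbalance has been seen carry less weight, particularly in an open-label trial.

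**Working it through.** **1. The plan's own figure.** The Sample size section assumes "60% of patients in the landiolol group reach the primary endpoint versus 40% of patients in the control group" and says "The sample size of 200 patients will provide 80% power to demonstrate a statistically significant difference". With 100 per group and two-sided alpha 0.05:

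- Power = Φ[(0.20·√100 − 1.96·√(2·0.5·0.5)) / √(0.6·0.4 + 0.4·0.6)] = Φ[(2.000 − 1.386)/0.693] = Φ(0.886) = 81.2%.
- The number needed for 80% is 97 per group.
- The exact power of the Newcombe rule (lower limit above zero) is 82.6%.

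The stated 80% reproduces, and the primary endpoint is not in question here.

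**2. Precision of the planned mortality comparison.** The documents give no mortality rate. Assuming 40% in both arms, the crude 95% half-width is 1.96·√(2·0.4·0.6/100) = 13.6 points. The Newcombe half-width is 12.6, 13.3 and 13.6 points at 30%, 40% and 50% mortality. Power for a 10-point reduction from those rates is 37%, 32% and 29%.

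**3. Gain from adjustment.** Trials of 100 per arm were simulated. The crude risk difference was compared with one standardised from a logistic model containing treatment and baseline severity. Prognostic strength is assumed and given as AUC.

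| Assumed mortality and covariates | AUC | SD crude | SD adjusted | Variance cut |
|---|---|---|---|---|
| 40% vs 30%, one score | 0.60 | 0.0658 | 0.0651 | 2% |
| 40% vs 30%, one score | 0.69 | 0.0664 | 0.0628 | 10% |
| 40% vs 30%, one score | 0.73 | 0.0672 | 0.0616 | 16% |
| 40% in both, three covariates | 0.64 | 0.0685 | 0.0666 | 5% |
| 40% in both, three covariates | 0.72 | 0.0694 | 0.0653 | 11% |
| 40% in both, three covariates | 0.77 | 0.0706 | 0.0628 | 21% |

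The one-score rows use 4,000 trials each, with log-odds 0.4, 0.7 and 1.0 per SD. The three-covariate rows use 5,000 trials each, with log-odds 0.3, 0.5 and 0.7 per SD for each covariate. The atrial fibrillation stratum was not simulated.

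For the three-covariate rows:

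- Sample-size equivalent: 1/0.946, 1/0.886 and 1/0.790, or about 6%, 13% and 27% more patients.
- Half-width (1.96 × SD): from 13.4 to 13.1, from 13.6 to 12.8, and from 13.8 to 12.3 points.

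In the one-score scenarios, power for the 10-point difference goes from about 31% to 32%, 34% and 35%.

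**4. Chance imbalance.** The difference in means of a standardised covariate has standard error √(2/100) = 0.141.

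- The probability of an imbalance above 0.2 SD in either direction is 2·[1 − Φ(0.2/0.141)] = 16%. An imbalance of 0.2 SD shifts the crude risk difference by 1.9, 3.0 and 4.0 points in the three one-score scenarios.
- At the 95% limit, 1.96 × 0.141 = 0.277 SD, the shifts are 2.6, 4.2 and 5.5 points.

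**5. Which covariates are secure.** Age and the norepinephrine rate at inclusion are eligibility items, so both are known before treatment. An entry SOFA score is not established. The eligibility item is an acute rise of at least 2 points that need not be present at inclusion, and the visible text does not say whether the day 1 score precedes treatment. The schedule figure is not available here.

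**The case against.** The strongest reply is that nothing here is an error. With 1:1 randomisation the crude comparison is valid, and chance imbalance is part of the sampling variation that the 95% interval already covers. The shifts of about 2 to 6 points lie well inside a half-width of about 13 points. The gain is small and rests wholly on assumed inputs. Mortality stays underpowered either way, and the article makes it supportive only. The SAP may also already hold a severity-adjusted analysis.

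Most of this stands, and it limits the point to efficiency and pre-specification. It does not remove the point. The article fixes the mortality method, and what it defers to the SAP is exploratory subgroup and sensitivity work, or alternatives if assumptions fail. Supportive evidence still benefits from data already in hand.

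A reader might infer more than the documents support:

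- **That the planned mortality result is biased.** Randomisation rules this out as a systematic effect.
- **That it is wholly unadjusted.** The CMH P value adjusts for atrial fibrillation; the interval, as described, does not.
- **That adjustment would remove imbalance.** It reduces the effect of imbalance in the measured covariates, as far as the model fits.
- **That mortality will be the headline or a formal safety result.** Table 3 lists it as a secondary endpoint, apart from the safety endpoints.
- **That a pre-treatment SOFA score is certainly on file.** The text leaves this open.

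**Conclusion.** The point holds as one of efficiency. The article ties ICU and 28-day mortality to an interval with no named covariates and a P value adjusted for atrial fibrillation only, while prognostic values known at entry go unused. Under assumed mortality of 30–40%, 100 patients per arm and a severity AUC of 0.60 to 0.77, adjustment would cut the variance of the risk difference by about 2% to 21%. In the three-covariate scenarios this narrows the half-width by about 0.4 to 1.5 points. The upper end needs three covariates that jointly predict death well; with age and norepinephrine rate alone the gain could lie nearer the lower end. The improvement is modest but nearly free. It does not call the validity of the planned comparison into question, and it gives no reason to replace that comparison.

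**What to change.** Before database lock, and before anyone examines mortality by arm, add to the SAP one covariate-adjusted analysis for each of ICU and 28-day mortality:

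- **Estimate:** a standardised risk difference from a logistic model, with its 95% confidence interval. Use this single measure. A conditional odds ratio is a different quantity and cannot be compared directly with the Newcombe difference.
- **Covariates:** atrial fibrillation stratum, age and norepinephrine rate at inclusion. Add SOFA only if a score taken before treatment is recorded.
- **Missing baseline values:** a simple rule stated in advance, such as single imputation from baseline data without regard to arm.
- **Reporting:** beside the planned Newcombe interval and CMH P value, labelled as supportive evidence.

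The cost is a short SAP addition and one extra model per endpoint. Age and norepinephrine rate need no new data collection.
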